#### Exit study criteria

2.1.3

A patient will be considered discontinued from the study only if they withdraw consent for follow-up at the participating center or are lost to follow-up after all means of contact have been exhausted. Surgical correction of angiomas during follow-up will not necessitate discontinuation from the study. In cases of discontinuation, the status of the patient at the last visit or last available contact will be used for the final analysis. Vital status may be ascertained through public records if all other means of contact fail.

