CCM lesions (number).CCM new lesions (number).Location of lesions (number of CCM lesions in each of the following sites: the cerebellum, the brainstem, the basal ganglia and thalami, the right cerebral hemisphere, and the left cerebral hemisphere).Radiological characteristics (size and number of CCM lesions) classified according to Zabramski classification: type I, II, III, and IV (7). The evolution of MRI markers, such as the number of new lesions, the size modification of lesions, and the signs of *de novo* bleeding, will be described. Changes over time will be assessed by means of generalized linear models with a Poisson distribution to account for the count nature of the data. Corrections for multiple testing will be applied to account for type 1 errors across multiple MRI outcomes. The assessment of changes over time will be performed for all patients included in the cohort as a change from baseline to 2-year follow-up.

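### The Poisson model named for MRI changes makes no allowance for overdispersed new-lesion counts or for pairing of baseline and 24-month lesion counts

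*Protocol article*

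**What the plan says.** The neuroimaging paragraph of Section 2.3.6.2 lists the number of lesions, the number of new lesions, lesion counts at five sites, and size and number by Zabramski type. These are to be assessed for the whole cohort and by relevant characteristics. The paragraph then says that the course of the MRI markers is to be described, and gives new lesions, changes in lesion size and new bleeding as examples. The sentence after that names the only inferential model for MRI data: "Changes over time will be assessed by means of generalized linear models with a Poisson distribution". The reason given is that the data are counts. Multiplicity is addressed ("Corrections for multiple testing will be applied to account for type 1 errors across multiple MRI outcomes"), and the assessment is to be "performed for all patients included in the cohort as a change from baseline to 2-year follow-up".

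Three other places bear on this:
- Section 2.1 says the cohort is meant to reflect the heterogeneity of the disease, from asymptomatic to high-risk patients, both children and adults. Section 2.1.1 admits mutations in any of three genes.
- Section 2.1.3 keeps operated patients in follow-up: "Surgical correction of angiomas during follow-up will not necessitate discontinuation from the study".
- The questionnaires paragraph of Section 2.3.6.2 names a repeated-measures method, repeated measures ANOVA. The MRI paragraph names none.

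**The concern.** There are two separate problems.

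The first concerns new lesions. Poisson standard errors are right only if the variance equals the mean. If patients differ in their underlying rate of lesion formation, the variance exceeds the mean and the model overstates its precision. The planned multiplicity correction takes the p-values as given, so it cannot repair p-values that are too small to begin with.

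The second concerns total and site-specific lesion counts. Each patient contributes a baseline and a 24-month value, and these share most of their lesions. A generalized linear model without clustering treats them as independent. If change is instead taken as a subtracted score, it can fall below zero after a resection, and a Poisson response cannot be negative. Either reading needs a correction.

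At stake is a stated secondary objective in Section 2.3.2: MRI markers of disease severity and progression. Markers could be declared associated with progression more often than the nominal error rate allows.

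**Working it through.** **Inputs from the article.** 100 patients with 8% dropout (Section 2.3.5). A 5.6% primary event proportion (Section 2.3.5). At least 55% expected to be active, meaning a CCM-related adverse event or at least 5 new lesions in 2 years (Section 2.3.6.2). The article gives no mean, variance or dispersion for lesion counts, and no figure for the Poisson analysis that could be reproduced. Its sample size does reproduce: 1.96² × 0.056 × 0.944 / 0.047² = 91.9, so 92, and 92/0.92 = 100. A median split of 92 evaluable patients gives 46 per group.

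**Step 1: is a pure Poisson distribution plausible?** Assume that between 55% − 5.6% = 49.4% (clinical events are the primary events only, with no overlap) and 55% (all active patients qualify on lesions) have at least 5 new lesions. Solving P(X ≥ 5) = 0.494 and 0.55 gives Poisson means of 4.6 and 4.9.

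| Quantity | Mean 4.64 | Mean 4.95 |
|---|---|---|
| P(no new lesion) = exp(−mean) | 1.0% (0.0097) | 0.7% |
| P(12 or more) | 0.3% | 0.5% |

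So almost every patient would form some new lesions and almost none would form many. That sits badly with a cohort chosen to span asymptomatic to high-risk disease.

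**Step 2: what overdispersion fits the same figure?** Take negative binomial counts with P(X ≥ 5) = 0.5 and variance/mean φ = 1 + mean/shape.

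| Shape | Mean | φ |
|---|---|---|
| 2 | 5.6 | 3.8 |
| 1 | 6.7 | 7.7 |
| 0.5 | 10.2 | 21 |

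The activity figure is compatible with φ = 1 and with all of these, so it does not fix the dispersion.

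**Step 3: effect on a two-group comparison.** The Poisson standard error is too small by a factor √φ, so the true two-sided level is 2[1 − Φ(1.96/√φ)] and the coverage of a 95% interval is one minus that.

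| φ | 1.96/√φ | True level | Coverage |
|---|---|---|---|
| 1 | 1.96 | 0.05 | 95% |
| 1.5 | 1.60 | 0.11 | 89% |
| 2 | 1.39 | 0.17 | 83% |
| 3.8 | 1.01 | 0.31 | 69% |
| 7.7 | 0.71 | 0.48 | 52% |

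Simulation with 46 against 46 patients and a mean of 5 new lesions agrees. The plain Poisson test rejected a true null in 5.1% of datasets with no overdispersion, 16% at shape 5 (φ about 2) and 29% at shape 2 (φ about 3.5). With an estimated dispersion (quasi-Poisson), rejection stayed between 4.7% and 5.4% in every scenario at this mean.

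**Step 4: total lesion counts, baseline against 24 months.** Assume 92 patients, a baseline mean of 20 lesions, 5 new lesions on average, and shapes from 0.5 to 2 for each. Fitted without clustering, the ratio of naive to true standard error ran from 0.72 to 1.34. With no true change and persistent lesions misread 5% of the time, rejection was about 0%. With independent Poisson counts around each patient's own rate, it was about 5%. The error therefore has no fixed direction.

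**The case against.** The strongest reply is that this is a condensed article. Naming the Poisson family does not exclude a scale parameter or robust errors, and such detail usually sits in an analysis plan that is not shown. That carries weight against any claim that overdispersion will certainly be ignored. It does not remove the point, because the article does more than stay silent: it names a specific model, and a better default is available at almost no cost.

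Several stronger readings are tempting, and the article does not support them.

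- *The Poisson model is applied to lesion size and bleeding.* A reader might infer this because the sentence about change follows directly on those markers and no other model is named. But the text says they will be described, and it justifies Poisson by the count nature of the data. The passage is ambiguous, not wrong.
- *Repeated measures are ignored throughout.* New lesions over 2 years is one count per patient, so no correlation problem arises there. The stated comparison is baseline to 2 years, not three correlated visits.
- *Standard errors are always too small.* This holds for overdispersed new-lesion counts. For paired totals the error can go either way (step 4).
- *The results will be wrong.* The dispersion is assumed. The 55% is a composite, and a pure Poisson distribution can reproduce it.
- *The model cannot handle a fall in lesion count.* That is true only of a subtracted response. With visit counts and a time term, a fall is simply a rate ratio below 1.

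It is also fair to say that the sentence on change concerns the whole cohort, and that no Poisson group test is spelled out. The same paragraph does, however, assess lesion characteristics by patient characteristics, so such comparisons are in scope.

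**Conclusion.** The point holds at moderate severity. A Poisson model without allowance for extra variation is a poor choice for new-lesion counts in this cohort. Comparisons by patient characteristics would reject too often if the variance exceeds the mean, which is very likely but not documented. The size rests on assumed dispersion: no inflation at a ratio of 1, about three times the nominal level at 2, about six times at 3.8 and between nine and ten times at 7.7. For total and site-specific counts, the unclustered model gives standard errors that are unreliable in either direction, and a subtracted change score does not suit a Poisson response once operated patients remain in the cohort. The primary endpoint and the sample size are not affected.

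**What to change.** Reword the neuroimaging paragraph of Section 2.3.6.2 as follows.

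- **New lesions:** negative binomial regression, or Poisson with robust or quasi-Poisson standard errors, with the log of the time between scans as an offset. Follow-up MRI may fall up to 40 days either side of the visit (Section 2.2.1), so intervals will differ between patients.
- **Total and site-specific lesion counts:** model the count at each visit with GEE or a mixed count model clustered by patient, not a change score, and state how resected lesions enter the count.
- **Scope:** say that the count model applies to counts only. State that size modification and de novo bleeding are either described only or analysed with models suited to their scale.

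The cost is a few sentences and a few lines of code before analysis. Intervals for new-lesion comparisons will usually be wider; for paired totals they may widen or narrow. No extra patients, scans or data are needed.

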In accordance with clinical practice, an annual brain MRI will be performed in the Neuroradiology Unit of the referral hospital, preferably on the same day as the clinical assessment. If this is not possible, the MRI will be scheduled within 1 month for the inclusion visit T0 and within ± 40 days for follow-up visits (T1-T2). The MRI protocol will include sagittal 3D T1-weighted turbo field echo, sagittal 3D T2-weighted turbo spin echo, sagittal 3D fluid-attenuated inversion recovery, axial diffusion-weighted imaging, axial susceptibility-weighted imaging, axial T2-weighted gradient echo, and optional diffusion tensor imaging and axial spoiled 3D multi-echo gradient-echo sequences (SGRE) for quantitative susceptibility mapping (QSM). The current protocol is in line with standard clinical practice. The collected MRIs will be centrally assessed at the MRI core laboratory of IRCCS Fondazione Ca′ Granda Ospedale Maggiore Policlinico by blinded personnel. The following MRI variables will be recorded at baseline and follow-up examinations: CCM lesion characteristics including number, signal (8), size, and location of CCMs and size modifications, signs of *de novo* bleeding, and number of *de novo* lesions at 12 and 24 months. Image examples of each Zabramski type of lesion will be provided to ensure that raters understand the Zabramski classification system. A standardized interpretation of MR imaging features on T1, T2, and SWI images that are relevant to classification will be discussed. Raters will independently classify a set of 15 MRI cases and then review any discrepancies. Interrater reliability will be assessed using a separate set of 30 MRI cases, which raters will classify independently while remaining blinded to each other’s assessments. Cohen’s kappa will be calculated.

Advanced MRI techniques such as diffusion tensor imaging (DTI) and QSM, which are not routinely performed in the follow-up of CCM patients, will be applied if available at the center and analyzed at IRCCS Fondazione Ca′ Granda Ospedale Maggiore Policlinico in the MRI core laboratory to assess iron deposition (3) and structural integrity. DTI and QSM do not require contrast media injection. This analysis does not impose any extra burden on patients, as they already undergo an annual MRI as part of clinical practice.

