#### Secondary objectives

2.3.2

To evaluate the new occurrence of other CCM-related clinical events, including seizures and recurrent headaches. Seizures, an important aspect of fCCMs, are assessed as a secondary endpoint rather than a primary endpoint, as their onset may be influenced by anti-convulsant therapy.To identify MRI biomarkers of disease severity and disease progression, including the number of CCM lesions, size of CCMs, signal of CCM lesions according to the Zabramski classification, lesion location, size modifications, signs of new bleeding, and the number of *de novo* CCM lesions at 12 and 24 months.To identify circulating biomarkers related to disease activity in fCCM subjects.To evaluate global cognitive function, disability, and health-related quality of life of fCCM patients.

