#### Sample size calculation

2.3.5

The primary endpoint, the new occurrence of CCM-related clinical events, defined as ICH and FNDs, excluding seizures, is expected in approximately 5.6% of the population based on the Treat_CCM trial (1). Assuming that 5.6% of subjects in the CCM_Italia cohort will develop a CCM-related clinical event, at least 100 patients (including a dropout of 8%) are needed to estimate this proportion with 95% confidence and 4.7% absolute precision.

According to the Treat_CCM study, 55% of fCCM patients are expected to experience increased disease activity. Dividing the population by the median level of a biomarker or imaging marker of interest (resulting in 2 groups of 50 individuals) would provide us a statistically significant result if the HR of this biomarker is at least 2.15 (power 80%, *α* = 0.05) (6, 7).

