#### Statistical analysis

2.3.6

Baseline characteristics will be presented for the total population and by relevant variables (e.g., sex, age categories, and number of CCM lesions). Relevant patient subgroups, such as gene mutation, age groups, and presence of baseline symptoms, will be compared by descriptive univariate statistics. Prior experience of the consortium has shown that data are quite complete, and imputation for missing values was not performed.

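### The modelled MRI change is set for the whole cohort as baseline to 2 years, but with 8% planned dropout not every patient can supply it, and the 12-month scan has no role in the model

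*Protocol article*

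**What the plan says.** The neuroimaging paragraph of section 2.3.6.2 fixes a population and an interval: "The assessment of changes over time will be performed for all patients included in the cohort as a change from baseline to 2-year follow-up". The method is given just before: "Changes over time will be assessed by means of generalized linear models with a Poisson distribution to account for the count nature of the data". No observation time is named for that model. The same paragraph also has a descriptive part, under which the evolution of the markers, including new lesions, size change and "the signs of *de novo* bleeding, will be described"; it names no time points.

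Other sections bear on this:

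- Section 2.3.2 lists among the MRI markers "size modifications, signs of new bleeding, and the number of *de novo* CCM lesions at 12 and 24 months". Section 2.2.1 records new lesions at the same two times.
- Section 2.3.5 sets the sample size at 100 or more, allowing for 8% dropout.
- Section 2.1.3 says that, for a patient who discontinues, the status at the last visit or contact goes into the final analysis. It does not mention MRI.
- Section 2.3.6 says that data were quite complete in the consortium's earlier experience and that "imputation for missing values was not performed".
- Section 2.2.1 prefers the MRI on the day of the visit and otherwise allows it "within 1 month for the inclusion visit T0 and within ± 40 days for follow-up visits (T1-T2").

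**The concern.** A change from baseline to 2 years needs a 2-year scan. The protocol plans for some patients to leave, so the stated population and the stated interval do not fit together. The patient this affects most has scans at baseline and 12 months and then leaves. That patient has a valid new-lesion count over one year, and the text supports two opposite treatments of it. With no imputation, the patient drops out of the model. With the last-status rule, the one-year count may stand in for a two-year count.

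New lesions accumulate with time, so the second treatment understates progression. The first discards data already collected, and it is biased if leavers progress at a different rate from stayers. Either way, the model makes no use of a scan that every patient still in follow-up at one year is due to have. For a study that aims to find imaging markers of progression, this is an avoidable loss.

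**Working it through.** **Inputs from the protocol article.** Expected proportion 5.6%, precision 4.7%, 95% confidence, 8% dropout, N = 100 (section 2.3.5); scans at baseline (T0), 12 months (T1) and 24 months (T2) (section 2.2.1).

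**Assumptions.** The documents give neither the timing of dropout nor the lesion rate of leavers. I vary both, with a constant lesion rate within each patient.

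**1. Reproduce the sample size.** n = z² p(1 − p) / d² = 1.96² × 0.056 × 0.944 / 0.047² = 91.93, rounded up to 92. Inflated for dropout: 92 / 0.92 = 100. The figure reproduces. The design therefore expects 92 patients with complete follow-up, and up to 8 of 100 cannot supply a baseline-to-2-year change.

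**2. Equal lesion rates, 12-month count taken as a 24-month count.** If k of the 8 leave after T1 and the rest leave before it, the observed mean as a fraction of the true 24-month mean is (92 + 0.5k) / (92 + k).

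- k = 4: 94 / 96 = 0.979, about 2% low.
- k = 8: 96 / 100 = 0.960, 4% low.

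Using completers only is unbiased here, at the cost of up to 8 patients. With k = 8, their T0–T1 intervals would add 8 patient-years to the completers' 184.

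**3. Leavers progress faster.** Let all 8 leave after T1, with r times the stayers' rate. In units of the stayers' mean:

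- true mean: (92 + 8r) / 100
- completers only: 1
- 12-month count as 24-month count: (92 + 4r) / 100
- log-time offset (total count over total time): (184 + 8r) / 192

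Each method as a fraction of the true mean:

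| r | True mean | Completers only | 12-month count as 24-month | Log-time offset |
|---|---|---|---|---|
| 1 | 1.00 | 1.000 | 0.960 | 1.000 |
| 2 | 1.08 | 0.926 | 0.926 | 0.965 |
| 3 | 1.16 | 0.862 | 0.897 | 0.934 |

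The two readings of the current text are 7.4% low at r = 2, and 13.8% or 10.3% low at r = 3. The offset model is 3.5% and 6.6% low. It roughly halves the bias at r = 2 and reduces it at r = 3, but does not remove it.

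**4. Scan windows.** Observation time also varies among completers. Taking 24 months as 730 days and the T0 window as running either side of the visit, the extremes are 730 − 30 − 40 = 660 days and 730 + 30 + 40 = 800 days, a ratio of 1.21. These are outer limits, since same-day scans are preferred and the T0 window may run in one direction only. The point only supports using actual scan dates.

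**The case against.** The strongest reply is that most of this is analysis-plan detail. Exposure time, the handling of a missing 2-year scan, and the choice between interval and cumulative counts are commonly left to an analysis plan or full protocol, and neither is shown. On this view the reference to the whole cohort only separates it from a subgroup, and taking 24 months as the modelled contrast while recording both scans is ordinary practice.

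Much of this stands. The lack of an offset in a condensed article is not a fault by itself, and a 24-month contrast is legitimate. What remains is that the article does not stay silent: it states a population and an interval that its own dropout figure makes incompatible. It also treats the questionnaires differently, giving them several time points and a repeated-measures method.

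A reader might infer more than the text supports:

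- **That the 12-month objective goes unanalysed.** The descriptive part of the neuroimaging paragraph can cover 12 months, and nothing there rules out a 12-month analysis. Only the modelled change omits it.
- **That carry-forward is prescribed.** Section 2.1.3 speaks of the patient's status and goes on to vital status. Applying it to lesion counts is an inference.
- **That imputation is ruled out for this study.** The sentence in section 2.3.6 is in the past tense and follows a remark on earlier experience.
- **That the subgroup comparisons in section 2.3.6 inherit the bias.** Those are descriptive comparisons in the paragraph on baseline characteristics, and no such link is shown.

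The replacement also needs care. Two intervals from one patient are correlated, and treating them as independent can understate standard errors. A log-time offset does not suit lesion size or Zabramski type.

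**Conclusion.** The point holds in a limited form. The population and interval stated for the modelled MRI change cannot both be met with 8% dropout. The text leaves open whether a patient with only baseline and 12-month scans is excluded or enters with a one-year count in place of a two-year count. The 12-month scan has no stated role in the model.

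This is a minor point on a secondary endpoint. With equal lesion rates the understatement runs from none (completers only) to 4% (all 8 carried forward). It reaches about 7% to 14% only if all 8 leave after the 12-month scan and progress two to three times faster than stayers. Both conditions are assumptions, so these figures show a range and do not predict a bias.

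**What to change.** For the count outcomes only (new lesions and new bleeds), replace the sentence in section 2.3.6.2 with wording to this effect:

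- Every patient with at least one follow-up MRI enters the count model, with log of the time between scans as offset.
- Each patient contributes either one cumulative count to the last scan, or interval counts (T0–T1 and T1–T2) with within-patient correlation handled by GEE or a random effect.
- Estimates are reported at 12 and 24 months. The interval version can give each year its own rate; the cumulative version reaches the 12-month estimate by assuming a constant rate.
- The last-status rule of section 2.1.3 does not turn a 12-month scan into a 24-month value.

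Lesion size and Zabramski type need their own wording, without this offset.

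The cost is a change of analysis text, since the scans are already planned and need only their dates. The drawback is that the model assumes leavers would have progressed like comparable patients who stayed. As the table shows, some bias remains if they would not have.

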## Discussion

3

In this study, a large number of adult and pediatric subjects affected by fCCMs will be observed for 24 months. Despite efforts in basic and clinical research and an improved understanding of the pathogenic mechanisms underlying the disease, predicting disease progression and identifying at-risk individuals and effective therapeutic targets remains challenging. This is particularly true for complex diseases, where genetic and environmental factors interact, and for rare conditions.

To tackle these challenges, this study will collect data that may help identify risk factors and disease trajectories. Moreover, we will collect information searching for specific biomarkers and imaging markers that could help identify at-risk patients and monitor disease progression and will combine expertise from various disciplines (biology, genetics, epidemiology, neurology, neurosurgery, and neuroradiology) to address the complexities of the disease.

The identification of biomarkers for disease progression is a crucial aspect in the management of multiple cerebral cavernous malformations (CCMs) and could also have significant implications for the treatment of sporadic malformations in terms of:

Monitoring disease progression: Reliable biomarkers can provide objective indicators of the disease status and its progression over time. This is particularly important for CCMs, which have a variable course. Improved quantification of disease progression may optimize the timing and methods of intervention and establish more effective follow-up protocols.Discovery of novel therapeutic targets: Biomarkers may reveal the pathogenic mechanisms underlying CCMs. A better understanding of the biological processes involved in the formation and progression of cavernous malformations may lead to the identification of new therapeutic targets.Establishment of personalized treatment: Identification of specific biomarkers and novel therapeutic targets may help the development of personalized treatment strategies. Biomarkers that indicate disease severity or the likelihood of hemorrhage can enable clinicians to tailor strategies based on individual patient characteristics. This approach may lead to a better selection of patients undergoing surgery and of those requiring closer monitoring, thereby improving clinical outcomes.Reduction of adverse events: In CCM patients, recurrent hemorrhages can result in significant disabilities and even death. Identifying biomarkers that indicate a high risk of complications, such as hemorrhage, enables the implementation of more effective preventive measures.Biomarker research can stimulate further clinical and preclinical studies, inform the design of innovative clinical trials, and create a virtuous cycle of scientific discovery and therapeutic improvement.

The significance of our project lies primarily in the dataset generated, which will represent the largest Italian prospective registry on the natural history of fCCMs assessed through combined approaches (e.g., clinical, MRI, and biochemical). Moreover, building on the biomarkers identified in the Treat_CCM clinical trial (#NCT03589014), this project will expand and validate the understanding of fCCMs.

Beyond the scope of the project, this dataset, which will continue to expand, will generate new insights into CCMs, improving clinicians’ expertise and patients’ treatment. The creation of a large standardized database will facilitate data access and promote collaborations among health professionals in case of future therapeutic trials. Including not only adults but also children with fCCMs in this observational cohort will expand knowledge about disease progression.

Moreover, the identification of biomarkers for disease progression is a fundamental step in guiding the clinical management of this challenging condition and enhancing clinical outcomes and quality of life. These biomarkers may also inform the treatment of sporadic malformations, a far more common condition.
